## 2.2 Scientific Rationale

### 2.2.1 Purpose of Study

The primary question that will be addressed in this ancillary study is whether SARS CoV-2 vaccines can prevent overall acquisition of infection and, therefore, have the ability to interrupt transmission. However, it is likely that some vaccinated individuals will continue to shed virus asymptomatically. Therefore, vaccine efficacy against the magnitude and duration of shedding will be included as exploratory aims, as these parameters can be considered to be proxies of reduced transmission potential, recognizing that definitive results require direct measurement of the frequency of infection in contacts of vaccinated compared to unvaccinated individuals.

### 2.2.2 Study Population

The pediatric expansion to the Phase 3 PREVENT-19 trial sponsored by Novavax is estimated to start enrollment in April-May 2021. The expansion will enroll ~3,000 adolescents (12-17 years of age). All children who are participating in the Phase 3 pediatric expansion trial are eligible for enrollment in the ancillary swab study. Approximately 75 sites are expected to participate in the pediatric expansion.

## **2.3 Potential Risks and Benefits**

### **2.3.1 Potential Risks**

Risks associated with this ancillary study are primarily associated with potential loss of confidentiality. The study team will make every effort to protect each participant's privacy and confidentiality. Participants will be assigned a unique study number (Subject ID) for all data and sample collection. Paper data collection forms and specimen labels will be identified only with Subject ID. Study files will be stored in locked file cabinets and electronic data collection and storage tools will be password protected. Access to participant data will be limited to authorized study personnel.

This study presents no greater than minimal risk to the participants. Risks associated with anterior nares nasal swab collection may include sneezing, eye watering, coughing, or possible epistaxis.

Notably, the ancillary swab study will be performed at the convenience of the Phase 3 study, where the goals of the Phase 3 study will take priority over this ancillary study (i.e., consideration for the Phase 3 study objectives and endpoints will supersede those of the ancillary study). The ancillary study is designed to generate additional valuable data on efficacy of SARS-CoV-2 rS/M1 vaccine against infection, including asymptomatic/very mildly symptomatic infection.

### **2.3.2 Potential Benefits**

There are no direct benefits to participants participating in this ancillary study; however, the results of this ancillary study may provide valuable information that can help others in the future.

---

## 3 STUDY DESIGN, OBJECTIVES AND ENDPOINTS OR OUTCOME MEASURES

### 3.1 Study Design Description

In this ancillary swab study, up to 3,000 participants who are participating in the PREVENT-19 Pediatric Expansion study and who provide informed consent/assent for the ancillary swab study will be sampled twice weekly starting at the day 21 visit, or as soon as possible thereafter, of the initial injection period until December 17, 2021 (~16-28 weeks) with nasal swabs for detection of SARS-CoV-2 infection by RT-PCR and incident infections tallied. Data sources from the Phase 3 trial (e.g., study product assignment, daily symptomatology) will be used in the ancillary study to estimate the vaccine efficacy against SARS-CoV-2 infection, including asymptomatic infection or mildly symptomatic infection not meeting the COVID-19 primary endpoint definition for the Phase 3 study. Longer infections with higher viral loads, as a proxy for transmission potential, will be captured in this design.

Participants in the PREVENT-19 Phase 3 trial (pediatric expansion study) are randomized to receive either SARS-CoV-2 rS/M1 vaccine or placebo (2:1 allocation) on days 0 and 21. The pediatric expansion study will have a “blinded-crossover” after ~3 months of follow-up after the completion of the initial set of vaccinations. Pediatric participants will be scheduled for administration of 2 injections of the alternate study material 21 days apart.

The study design will allow a comparison of the incidence and other characteristics of SARS-CoV-2 infection in recipients of vaccine versus placebo. In addition, we have amended the initial design to continue swabbing after the blinded cross-over occurs and all participants are vaccinated. The cross-over coincides with the emergence of the delta Variant of Concern (VOC) when the rate of breakthrough infections is expected to increase. By extending swabbing, we will be able to assess the duration of vaccine efficacy by comparing the incidence and characteristics of break-through infection among participants who were vaccinated in April-June to those who were vaccinated in August-September 2021.

### 3.2 Study Objectives

#### 3.2.1 Primary

- To estimate the efficacy of SARS-CoV-2 rS/M1 vaccine against infection

### **3.2.2 Secondary**

- To estimate the efficacy of SARS-CoV-2 rS/M1 vaccine against asymptomatic/ very mildly symptomatic infection
- To determine the durability of efficacy of SARS-CoV-2 rS/M1 vaccine against infection
- To determine the durability of efficacy of SARS-CoV-2 rS/M1 vaccine against asymptomatic/very mildly symptomatic infection

### **3.2.3 Exploratory**

- To determine the sequence of breakthrough SARS-CoV-2 infections
- To estimate the VE on duration of infection
- To estimate the VE against SARS-CoV-2 viral load as a proxy of transmission
- To estimate the efficacy of SARS-CoV-2 rS/M1 vaccine against a composite outcome of asymptomatic/ very mildly symptomatic infection plus pre-symptomatic infection
- To explore whether observed VE against COVID-19 illness reflects a transition from symptomatic into asymptomatic infections versus an absolute reduction in all SARS-CoV-2 infections

## **3.3 Study Endpoints or Outcome Measures**

### **3.3.1 Primary**

- Reverse transcriptase polymerase chain reaction (RT-PCR)-confirmed SARS-CoV-2 infection detected in nasal swabs collected twice weekly from the day 21 visit or thereafter, until ancillary study end in the vaccine group and the placebo group

### **3.3.2 Secondary**

- RT-PCR-confirmed SARS-CoV-2 infection detected in nasal swabs collected twice weekly from the day 21 visit or thereafter, until ancillary study end, without COVID-19 illness as defined in the primary Phase 3 study endpoint
- RT-PCR-confirmed SARS-CoV-2 infection detected in nasal swabs collected twice weekly from the crossover dose 2 visit (or thereafter) until ancillary study end among the group who initially received vaccine compared to the group who initially received placebo

- 
- RT-PCR-confirmed SARS-CoV-2 infection detected in nasal swabs collected twice weekly from the crossover dose 2 visit (or thereafter) until ancillary study end among the group who initially received vaccine compared to the group who initially received placebo without COVID-19 illness as defined in the primary Phase 3 study endpoint

### 3.3.3 Exploratory

- Viral genome sequence of PCR-positive samples
- Duration of shedding as indicated by RT-PCR in vaccinated vs placebo recipients
- Reduction in viral load (and perhaps subgenomic RNA), as a proxy for transmission, in PCR-positive samples from vaccinated vs placebo recipients
- Proportion of days that are symptom-free on days that positive swabs are collected
- Ratio of asymptomatic to symptomatic infections in vaccinated vs placebo recipients. Data on symptomatology will be extracted from the Phase 3 trial database, which will be separate but linkable to the ancillary study database.

---

## **4 STUDY INTERVENTION/INVESTIGATIONAL PRODUCT**

Study participant will be randomized to receive either SARS-CoV-2 rS/M1 vaccine or placebo (2:1 allocation) on days 0 and 21 as part of the parent PREVENT-19 trial. In the current protocol, no interventional product will be administered. Each participant's blinded allocation will be accessed through the PREVENT-19 trial database during analysis.

---

## **5 SELECTION OF SUBJECTS AND STUDY ENROLLMENT AND WITHDRAWAL**

Subject Inclusion and Exclusion Criteria must be confirmed by a study clinician licensed to make medical diagnoses.

No exemptions will be granted on Subject Inclusion/Exclusion Criteria.

### **Eligibility Criteria**

#### **5.1.1 Subject Inclusion Criteria**

Each participant must meet all of the following criteria to be enrolled in this study:

1. Participant in the parent study
2. Less than 18 years and  $\geq 12$  years of age at time of enrollment
3. Ability and willingness to give informed consent/assent prior to study enrollment and comply with the study procedures
4. Received two doses of study product
5. Providing surveillance data on COVID-19 symptoms as described in the parent protocol
6. Access to a cell phone or Wi-Fi/Camera enabled device with ability to download and use the MG Scanner™ Application
7. Active independent or unique email address

#### **5.1.2 Subject Exclusion Criteria**

Participants meeting the following criterion will be excluded from the study:

1. Any condition that would, in the opinion of the investigator, place the participant at an unacceptable risk of injury or render him/her unable to comply with the study requirements.

---

## **5.2 Withdrawal from the Study, Discontinuation of Study Product, or Study Termination**

### **5.2.1 Withdrawal from the Study or Discontinuation of the Study Product**

Subjects may voluntarily withdraw their consent for study participation at any time without penalty or loss of benefits to which they are otherwise entitled.

An investigator may also withdraw a subject from participating in the study for any reason. If a subject withdraws or is withdrawn prior to completion of the study, the reason for this decision must be recorded in the case report forms (CRFs).

The reasons, might include, but are not limited to the following:

- Subject no longer meets eligibility criteria
- Subject becomes noncompliant
- Medical disease or condition, or new clinical finding(s) for which continued participation, in the opinion of the investigator might compromise the safety of the subject, interfere with the subject's successful completion of this study, or interfere with the evaluation of responses
- Subject lost to follow-up
- Subject unblinded in parent study

The investigator will inform the participant that already collected data will be retained and analyzed even if the participant withdraws from this study.

### **5.2.2 Subject Replacement**

Subjects who withdraw, or are withdrawn from this study, or are lost to follow-up after signing the informed consent form (ICF) will not be replaced.

### **5.2.3 Study Termination**

If the study is prematurely terminated by the sponsor, any regulatory authority, or the investigator for any reason, the investigator will promptly inform the study subjects and assure appropriate therapy or follow-up for the subjects, as necessary. The investigator will provide a detailed written explanation of the termination to the IRB/IEC.

---

## 6 STUDY PROCEDURES

### 6.1 Screening

Participants in the Phase 3 trial will have the ancillary study explained to them by study personnel during their day 21 visit or at another study encounter. If contact at the day 21 visit is not possible, a later appointment may be arranged for enrollment into the ancillary swab study. Those with expressed interest, will provide informed consent/assent prior to any study procedures. The consent form will include permission for investigators to review the participant's research records and to link with the parent study database at the appropriate time to obtain related information on randomization assignment, COVID-19 symptomatology, and RT-PCR results from study-specific swabs or other relevant events.

Informed consent/assent is required prior to enrollment and prior to any study-related procedures. Parental or guardian permission will be obtained for all children. Assent will be obtained from children according to the IRB requirements at each site. To ensure that the participant's rights are protected and that all study participants receive, read, have explanation of and sign an informed consent/assent prior to enrolling in this study, research team members will follow the informed consent process outlined in site-specific SOPs and as approved by the single IRB, as applicable.

Following the attainment of informed consent/assent, eligibility criteria will be reviewed. The screening visit will occur concurrently with enrollment in most cases. A window of 7 days between screening and enrollment is allowed.

### 6.2 Enrollment

After obtaining informed consent/assent as above, study staff will collect a limited array of demographic and clinical information from the participant. An application will be downloaded onto the participant's or participant's parent's smart phone or Wi-Fi/camera enabled device that will permit the participant to scan the bar code on nasal swab vials at home prior to sending them to the ancillary swab study central laboratory at the University of Maryland School of Medicine (UMSOM)/Institute for Genome Sciences (IGS) for SARS CoV-2 RT-PCR testing and storage. The application will log the date/time of each sample collection during the home swabbing period. No Protected Health Information (PHI) will be transferred through the application. Study personnel will instruct the participant on the methods for self-collection and shipment of nasal swab specimens. Participants will receive a packet of swab kits for their home use.

If the participant/participant's parent does not have an appropriate device available, University of Maryland will provide Wi-Fi and camera enabled devices for participants to use the MG Scanner mobile application to track their bi-weekly swabs. These devices will not have active cellular service or data plans. The devices will not be offered to all participants. They will be provided only to those who do not have a personal device that is capable of downloading and using the MG Scanner mobile application, or parents who do not have an adequate number of devices to accommodate the participants in their household (multiple siblings enrolled). Study devices will be shipped overnight from the University of Maryland to the participants home directly after enrollment. Site coordinators will assist study participants with the final app registration steps after confirmation that they have received their study device. The helpline will also be available to participants for any questions or concerns with downloading and setting up the MG Scanner application on the study devices. Devices will not be collected or returned at the end of the study.

### **6.3 Twice Weekly Swab Self-Collection at Home**

Beginning as soon as possible, on or after day 21, or soon thereafter, (week 1 in Appendix A), the participant will self-collect an anterior nares nasal swab for SARS CoV-2 RT-PCR testing twice weekly. If the child is not able to self-collect independently, collection may be performed by the parent or by the child under parental supervision. For example, each participant will collect a swab on the Monday (+1) and Thursday (+1) of each week. The duration of nasal swabbing for each participant cannot be determined with precision at this time; it might range from approximately 16-28 weeks depending on when the participant was enrolled. Home nasal swabs will be retrieved by a courier and/or mail delivery service and delivered to the UMSOM/IGS laboratory.

Reminder e-mails will be sent on the day of expected sample collection. If a swab is missed, the participant/participant's parent will receive a phone call reminder. As this is a research study, the results of these tests will not be released to the participant/parent.

### **6.4 MG Scanner Application**

The MG Scanner application is an internally developed mobile application for iOS and Android devices. The application is designed to facilitate the registration of participants for COVID-19 testing through indirect interaction with the Zoran system. MG scanner also provides functionality for the scanning and registration of collected samples for testing.

---

In this system the user registers his/her device through the application via an emailed invitation. This registration binds the device ID to the participant's medical record number (MRN). The MRN is unique to each individual and an individual only has one MRN in the Zoran system. This MRN is separate from the participant's hospital/clinic MRN or the parent study ID. The user can then submit a sample for testing through a sample scanning component of the app. The app will scan two globally unique IDs from pre-labeled sample collection tubes and those IDs will be bound to the participant MRN as a pending specimen. Scanning of two globally unique IDs ensures the tube only occurs once and is positively associated with the participant MRN. If one barcode is damaged during the collection or transport process the specimen can still be positively associated with the submitting participant.

## 6.5 Final Study Visit

The final ancillary study swab will be collected by December 17, 2021 at which point the participant's ancillary study participation will be completed (Appendix).

## 6.6 Protocol Deviations

A protocol deviation is any noncompliance with the clinical trial protocol, GCP, or protocol-specific Manual of Procedures (MOP) requirements. Failure of a participant to collect nasal swabs at home or collection outside of the window will not be captured as protocol deviations as it will not impact study safety or overall scientific integrity. The noncompliance may be either on the part of the subject, the investigator, or the study site staff. As a result of deviations, corrective actions should be developed by the site and implemented promptly. It is the responsibility of the site Principal Investigator and other study personnel to use continuous vigilance to identify and report protocol deviations. All individual protocol deviations will be addressed in subject study records. All protocol deviations, either individual, product, or site-specific will be collected and the record stored in a sponsor-determined location. Protocol deviations must be sent to the local IRB/IEC per its guidelines. The site Principal Investigator and other study personnel are responsible for knowing and adhering to their IRB/IEC requirements.

---

## **7 DESCRIPTION OF CLINICAL AND LABORATORY EVALUATIONS**

### **7.1 Laboratory Evaluations**

#### **7.1.1 Research Assays**

At the enrollment visit, each participant will be provided kits for collection containing tubes and swabs along with collection instructions in each kit. They will be instructed on the proper method of obtaining nasal swabs during the visit. Additionally, the participants will be shown how to register with the application (MG Scanner™) to log each sample when it is collected.

At each required timepoint, the participant or his/her parent will collect an anterior nares nasal specimen of nasal secretions by swabbing the anterior nares of each nostril according to detailed standardized procedures demonstrated in the provided instructions. The swab will be placed in a vial containing buffer solution and maintained at room temperature.

The application will log the date/time of each sample collection during the observation period.

The swabs will be sent to the University of Maryland School of Medicine, Institute of Genome Sciences (UMSOM/IGS) laboratory for analyses.

##### **7.1.1.1 Laboratory Specimen Preparation, Handling, and Storage**

Samples will be shipped to UMSOM/IGS and will be run as they are received. Stability studies have demonstrated that all sample storage and shipping can be done at room temperature without affecting the SARS-CoV-2 RT-PCR test performance.

##### **7.1.1.2 Laboratory Specimen Shipping**

Participants will package collected swabs according to the provided instructions in provided shipping envelopes or boxes addressed to the UMSOM/IGS laboratory. Shipping to the UMSOM/IGS laboratory will occur every 1-2 weeks.

## **8 ASSESSMENT OF SAFETY**

### **8.1 Assessing and Recording Safety Parameters**

#### **8.1.1 Adverse Events (AEs) Reporting**

No adverse reactions are anticipated in this study, and the study procedures present no anticipated risks beyond the completion of the study. It is anticipated that the participants may experience discomfort when anterior nares nasal swab specimens are being collected; however, the risks and discomfort in this study are not greater than those ordinarily encountered during the routine collection of the anterior nares nasal swabs at a clinician's office.

Vaccine related AEs will not be collected as part of this ancillary study. The Sponsor will collect AE information via the CRF. AEs that last greater than 15 minutes will be collected from the time of swab collection to the time that the subject completes the study. Such data collection will include the start and stop dates of the event, causality with the swab collection (not related, related), outcome (ongoing, recovered, recovered with sequelae, not recovered, fatal), code for seriousness (SAE, not serious), and intensity (mild, moderate, or severe). Only events that are moderate or severe in intensity will be recorded. The definitions of mild, moderate, or severe are as follows:

- 1 = Mild (awareness of a symptom but the symptom is easily tolerated)
- 2 = Moderate (discomfort enough to cause interference with usual activity)
- 3 = Severe (incapacitating; unable to perform usual activities; requires absenteeism or bed rest)

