## 9 HUMAN SUBJECTS PROTECTION

### 9.1 Institutional Review Board/Independent Ethics Committee

Each site principal investigator will obtain IRB approval for this protocol to be conducted at his/her research site(s) and send supporting documentation to the DMID before initiating recruitment of subjects. The investigator will submit applicable information to the IRB/IEC on which it relies for the review, to conduct the review in accordance with 45 CFR 46, ICH E6 GCP, and as applicable, 21 CFR 56 (Institutional Review Boards) and 21 CFR 50 (Protection of Human Subjects), other federal, state, and local regulations. The IRB/IEC must be registered with OHRP as applicable to the research. DMID must receive the documentation that verifies IRB/IEC-approval for this protocol, associated informed consent documents, and upon request any recruitment material and handouts or surveys intended for the subjects, prior to the recruitment and enrollment of subjects.

Any amendments to the protocol or consent materials will be approved by the IRB/IEC before they are implemented. IRB/IEC review and approval will occur at least annually throughout the enrollment and follow-up of subjects and may cease if annual review is no longer required by applicable regulations and the IRB/IEC. The investigator will notify the IRB/IEC of deviations from the protocol and reportable SAEs, as applicable to the IRB/IEC policy.

Each institution engaged in this research will hold a current Federalwide Assurance (FWA) issued by the Office of Human Research Protection (OHRP) for federally funded research.

A single IRB of record, WCG IRB, will be accountable for compliance with regulatory requirements for this multi-centered study, at participating sites. Written reliance agreements between the single IRB and participating sites will be required. The reliance agreements will set forth the specific responsibilities of the IRB and each participating site. Participating sites will then rely on the IRB of record to satisfy the regulatory requirements relevant to the IRB review. The participating sites will maintain essential required documentation of IRB reviews, approvals, and correspondence, and must provide copies of any agreements and essential documentation to the DMID or regulatory authorities upon request.

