## **8. SAFETY ANALYSES**

Limited safety data were collected as part of the SNIFF study and are expected to be low in frequency. If applicable, summaries of adverse events will include a cumulative listing of adverse events and a table displaying the total number of adverse events by severity grade and relationship to study product.

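### The duration and intensity limits on adverse event recording in Protocol v4.0 section 8.1.1 make no exception for serious events

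*Supplement*

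**What the plan says.** Protocol v4.0 section 8.1.1 sets two conditions. On duration: "AEs that last greater than 15 minutes will be collected". On intensity: "Only events that are moderate or severe in intensity will be recorded". Between the two, the paragraph lists the items to be collected for each event. They include a "code for seriousness (SAE, not serious), and intensity (mild, moderate, or severe", and an outcome code that runs as far as fatal. The grades are then defined, beginning with "1 = Mild (awareness of a symptom but the symptom is easily tolerated". No sentence says how the two conditions apply to a serious event, and the section does not define one.

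Two other places in Protocol v4.0 mention serious events. Section 9.1 says: "The investigator will notify the IRB/IEC of deviations from the protocol and reportable SAEs, as applicable to the IRB/IEC policy". Section 13.3 says that adverse event data, serious ones included, are entered in the electronic case report form.

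SAP v2.0 section 8 plans, if applicable, a listing and a table showing "the total number of adverse events by severity grade". It does not mention either recording limit.

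**The concern.** Seriousness and intensity are different properties, and section 8.1.1 codes them in separate fields. A limit on intensity is therefore not a limit on seriousness, and a duration limit is unrelated to both. Without an exception, the section asks for a seriousness code but does not guarantee that every serious event is recorded.

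There is also a plain contradiction on mild events: the grade is listed among the values to collect and is defined, and then events of that grade are not to be recorded.

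What is at stake is the completeness of the study's own safety record. Section 8.2 provides for no safety committee and leaves oversight to the Principal Investigator, so this recording rule decides what the study database can show. An event screened out under the rule leaves no adverse event entry, and the database cannot reveal how many there were.

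**Working it through.** The plan states no figure to reproduce, and no power or event calculation applies. The check is to apply both sentences of section 8.1.1 literally to every combination of its own categories.

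Inputs, all from section 8.1.1: duration (15 minutes or less, more than 15 minutes), intensity (mild, moderate, severe) and seriousness (serious, not serious). That gives 2 × 3 × 2 = 12 combinations.

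| Duration | Intensity | Serious: recorded? | Not serious: recorded? |
|---|---|---|---|
| 15 min or less | mild | no | no |
| 15 min or less | moderate | no | no |
| 15 min or less | severe | no | no |
| more than 15 min | mild | no | no |
| more than 15 min | moderate | yes | yes |
| more than 15 min | severe | yes | yes |

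- Recorded: 1 duration × 2 intensities × 2 seriousness values = 4 of 12.
- Serious combinations: 6. Recorded: 2. Not recorded: 3 (brief, any intensity) + 1 (longer but mild) = 4.
- Mild combinations: 2 durations × 2 seriousness values = 4, none recorded. If the table in SAP section 8 is laid out on the protocol's three grades, the mild category is empty by rule.

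These are counts of rule combinations. They say nothing about how often each occurs.

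Next, does any other text restore the lost serious combinations?

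- Section 9.1 covers notification to the ethics board of reportable serious events, as that board's policy requires. It does not say that those events enter the study's adverse event data, or that the limits in 8.1.1 are set aside.
- Section 13.3 says how adverse event data reach the electronic form. It does not say which events qualify.
- SAP section 8 summarises what was recorded and cannot recover what was not.

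None of these overrides section 8.1.1, so the four serious combinations stay outside the record on a literal reading.

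**The case against.** The strongest reply is that this is a gap in wording with little practical reach. No study product is given, the protocol classes the study as minimal risk, and no objective or endpoint concerns safety. The limit on intensity was added deliberately in version 2.0, and sparing sites the work of recording trivial discomfort is a fair choice. An event with a serious outcome would ordinarily last more than 15 minutes and interfere with usual activity, and so would pass both limits. All of this stands. It makes the affected events uncommon, but it does not supply the missing exception.

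A reader might infer more than the documents support:

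- *That the limits remove most of the risks the protocol names.* Section 2.3.1 says: "Risks associated with anterior nares nasal swab collection may include sneezing, eye watering, coughing, or possible epistaxis". It gives no duration, intensity or frequency for any of the four. Depending on what is assumed, the share removed is anywhere from 0 of 4 to 4 of 4.
- *That events leading to withdrawal are lost.* Section 5.2.1 requires the reason for withdrawal in the case report form, with no limit on duration or intensity, and SAP section 6.1.3 tabulates reasons for non-completion by arm.
- *That an empty mild category will be taken for good tolerability.* SAP section 8 applies only if applicable and names no mild row, so this is conjecture. The modest point that remains is that the table should state what it covers.
- *That sections 8.1.1 and 9.1 conflict.* They impose different duties. Both can be followed, and the gap in the study data is still there.

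**Conclusion.** The point holds as a gap in the recording rule. Followed literally, section 8.1.1 leaves a serious event out of the study's adverse event data if it lasts 15 minutes or less at any intensity, or lasts longer but is graded mild: 4 of the 6 serious combinations. The section also contradicts itself on whether mild is a recorded grade.

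The number of events involved cannot be computed, because the documents give no event rate. It is probably small. That rests on the assumption that most serious events are neither brief nor mild, which is reasonable but cannot be checked here because section 8.1.1 does not define a serious event. Nothing in the documents shows that a serious event was actually missed. The infection endpoint and the vaccine efficacy estimate do not depend on this rule. The case for acting is that the correction is cheap and keeps the sponsor's limit on routine mild events.

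**What to change.** In Protocol section 8.1.1:

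- Add one sentence: serious events are recorded whatever their duration or intensity.
- State that the duration and intensity limits apply to non-serious events only.
- Reconcile the mild code with the rule. Once serious events are exempt, mild remains a possible grade for them, so the section should say that the code is used for serious events only.

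The recorded combinations then become 6 serious + 2 non-serious = 8 of 12. The 4 left out are all non-serious.

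In SAP section 8, label the table as covering moderate or severe events lasting more than 15 minutes plus all serious events. Section 6.5 ends swabbing by 17 December 2021, so the recording rule can no longer be changed for this cohort. If sites applied section 8.1.1 as written, the label should leave out the words about all serious events, and the report should state the limits as a limitation.

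The cost is one protocol sentence, two small clarifications, a table label and a few more case report form entries. Routine mild or brief discomfort is still not collected.
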